## Abstract

**Background:**

There is as yet no evidence on the feasibility of implementing recommendations from the National Institute of Health and Care Excellence (NICE) osteoarthritis (OA) guidelines in primary care, or of the effect these recommendations have on the condition. The primary aim of this study is to determine the clinical and cost effectiveness of a model OA consultation (MOAC), implementing the core recommendations from the NICE OA guidelines in primary care. Secondary aims are to investigate the impact, feasibility and acceptability of the MOAC intervention; to develop and evaluate a training package for management of OA by general practitioners (GPs) and practice nurses; test the feasibility of deriving ‘quality markers’ of OA management using a new consultation template and medical record review; and describe the uptake of core NICE OA recommendations in participants aged 45 years and over with joint pain.

**Design:**

A mixed methods study with a nested cluster randomised controlled trial.

**Method:**

This study was developed according to a defined theoretical framework (the Whole System Informing Self-management Engagement). An overarching model (the Normalisation Process Theory) will be employed to undertake a comprehensive ‘whole-system’ evaluation of the processes and outcomes of implementing the MOAC intervention. The primary outcome is general physical health (Short Form-12 Physical component score [PCS]) (Ware 1996). The impact, acceptability and feasibility of the MOAC intervention at practice level will be assessed by comparing intervention and control practices using a Quality Indicators template and medical record review. Impact and acceptability of the intervention for patients will be assessed via self-completed outcome measures and semi-structured interviews. The impact, acceptability and feasibility of the MOAC intervention and training for GPs and practice nurses will be evaluated using a variety of methods including questionnaires, semi-structured interviews, and observations.

**Discussion:**

The main output from the study will be to determine whether the MOAC intervention is clinically and cost effective. Additional outputs will be the development of the MOAC for patients consulting with joint pain in primary care, training and educational materials, and resources for patients and professionals regarding supported self-management and uptake of NICE guidance.

**Trial registration:**

ISRCTN number: ISRCTN06984617.

**Electronic supplementary material:**

The online version of this article (doi:10.1186/s13012-014-0095-y) contains supplementary material, which is available to authorized users.

## Background

There is a perception that osteoarthritis (OA) is a ‘natural’ part of ageing and there are limited interventions available [1,2]. Whilst there are many published guidelines on the treatment of OA [3-10] there is a gap between the care that is recommended and the care that patients receive [11,12]. NICE have recommended that all patients with OA should be offered three core treatments when they first present in primary care (see Figure 1): education and access to information; advice on local muscle strengthening exercise and general aerobic fitness; and, if appropriate, advice on losing weight [13].

**Figure 1 Fig1:**
[figure not shown]
**National Institute for Health and Clinical Excellence (NICE) osteoarthritis treatment recommendations (Conaghan et al.** [10]**).** Reproduced from, Care and management of osteoarthritis in adults: summary of NICE guidance, Conaghan P, Dickson J, Grant R, 336, 502-503, 2008, with permission from BMJ Publishing Group Ltd.

For patients and healthcare professionals (HCPs) in primary care, the clear message that emerges from the guidelines is that there is a range of simple interventions for which there is evidence of clinical effectiveness. By contrast, there is clear evidence that the core aspects of assessment and management of OA as currently delivered in primary care do not meet the recommendations of these guidelines [11]. Two recent Delphi consensus exercises have been conducted to address the limited research evidence on the content of a model OA consultation during which the core package of care could be delivered [14,15]. However, there is as yet no evidence on the feasibility of using this model consultation as a way of implementing NICE core OA treatments in primary care and the effect of this support for self-management on the course and impact of the condition.

The importance of self-management for long term illnesses and of professional support for self-management are emphasised in NHS policy [16]. Studies have shown that among patients consulting for knee OA, core treatments were mostly self- rather than doctor-initiated [1,11]. Previous research suggests that patients need more information about OA to enable them to manage their condition more effectively [17]. Lay ideas of self-management include minimising the impact of conditions [18,19], maintaining a sense of ‘normality’ [18,20], and maintaining social roles and obligations [21,22].

The way in which complex interventions, such as supported self-management approaches, are developed and then become embedded in routine clinical practice needs to be supported by theoretical models and evaluated appropriately [23]. A specific model of support for self-management called the ‘Whole system Informing Self-management Engagement’ (WISE) model [24] is predicated upon the argument that for self-management support to be effective, it requires the understanding and incorporation of the patient agenda into the consultation, including what they are already doing. A whole systems approach is needed, which engages with practitioners and service organisations as well as the patient [24]. The WISE model has been used in a number of long-term illnesses [25-27], and envisages informed patients receiving support and guidance from trained practitioners who are working within a healthcare system that is geared up to be responsive to patients’ needs.

Michie and colleagues have produced a synthesis of psychological theories to enable design and implementation of behaviour change interventions [28-30], and Grol and colleagues have developed a useful framework for translating evidence into practice [31]. The Calgary-Cambridge framework has specifically been developed to enhance consultation skills [32]. The Normalisation Process Theory (NPT) [33,34] is a sociological theory concerned with understanding and evaluating how complex interventions become embedded in routine clinical practice. These approaches will be integrated to develop the model OA consultation (MOAC) intervention and the HCP training in this study.

This study is focused on determining the current management of OA in consultations and whether supported self-management, delivered in a model OA consultation, could offer a clinically practicable approach to implementing the core NICE recommendations. We will undertake a cluster randomised controlled trial (RCT) to evaluate the whole systems approach and to determine the clinical and cost effectiveness of the MOAC intervention. The protocol has been reported using the SPIRIT recommendations [35,36].

### Aims

The primary aim of the study is to:Determine the clinical and cost effectiveness of the MOAC intervention in patients with OA.

Secondary aims are to:Describe the uptake of core NICE OA recommendations in participants aged 45 years and over with joint pain;Test the feasibility of deriving ‘quality markers’ of OA management using a new consultation template and medical record review;Develop and evaluate a training package for management of OA by general practitioners (GPs) and practice nurses;Investigate the impact, feasibility and acceptability of the MOAC intervention.

### Design

The MOSAICS study is a mixed methods study with a nested cluster RCT based in eight general practices, comprising of four components (see Figure 2).

**Figure 2 Fig2:**
[figure not shown]
**MOSAICS study overview.**

### Participants

HCPs and their respective practice populations from eight general practices will be invited to participate and randomly allocated to two clusters: ‘intervention’ and ‘control’ practices. The practice populations of the practices recruited, aged 45 years and over, will form the sampling frame for the overall study. The eligibility criteria for the study are described in Table 1. Resources to support primary care engagement are described in Additional file 1.

**Table 1 Tab1:** **MOSAICS study eligibility criteria**

**Eligibility criteria**	
**General practices and health-care professionals**	• Member of the Central England PCRN or a Keele Research Network Practice
	• At least two GPs willing to undertake the study as per protocol, *i.e*., act as a control or intervention practice
	• Willing, and able, to allow one (or for preference two – to allow for cross cover) of their practice nurses to be trained to deliver the MOAC 2 clinics
	• Able to physically accommodate the nurse clinics in the practice
	• Uses the EMIS computerised consultation system
	• Nurses and GPs consenting to follow up by the MOSAICS study team
	• GPs willing to be trained to carry out the MOAC 1 consultations
	• Nurses willing to be trained to carry out the MOAC 2 clinics
	• Nurses who consent to being observed and audio recorded in MOAC 2 clinics
***Patients**	Inclusion Criteria:
	• Males and Females
	• 45 years and over
	• Registered with a MOSAICS study practice
	• Consenting to further contact from the study team and medical record review (consent sought as part of the Patient Population Survey)
	Exclusion Criteria:
	• Excluded via GP screen of practice list
	• Unable to give fully informed consent, *e.g*., learning difficulties or dementia
	• Resident in a care or nursing home
	• History of serious disease, *e.g*., malignancy, terminal illness
	• Unable to consult in the general practice
	• Flagged as excluded from research in that practice

EMIS = Egton Medical Information System; GP = General Practitioners; MOAC = Model Osteoarthritis Consultation; MOSAICS = Management of Osteoarthritis In consultations; OA = Osteoarthritis; PCRN = Primary Care Research Network.

*All patients registered with MOSAICS practices randomised to the intervention arm of the study had access to the MOAC 1 and MOAC 2 clinics, including those who did not consent to be followed up, as these ran as part of normal clinical care within each intervention practice.

### Ethics approval

The study has been approved by the North West 1 Research Ethics Committee, Cheshire (REC reference: 10/H1017/76).

### Consent

Informed consent will be obtained from all HCPs and patients participating in the study (see Additional file 2).

### Components of the MOSAICS study

The cluster randomised controlled trialPopulation surveyConsultation template and medical record reviewEvaluation of the MOAC intervention and the training

### Study component 1: The cluster RCT

This will be a two-arm prospective pragmatic cluster RCT based in eight general practices in the North West midlands and Cheshire, UK. This trial will test the hypothesis that the MOAC intervention is superior to control and will be a parallel group longitudinal design with repeated measures. Practices will be randomly allocated to two clusters: ‘intervention’ and ‘control’ practices. Stratified block randomisation will be performed with the practices stratified into four largest and four smallest practices by list size. In each stratum, the practices will be randomly allocated by a computerised random number generator using blocking with two practices per study group.

Recruitment to the trial will occur over a six-month period. All practices will use the OA template and will be given standard information on OA for patients and healthcare professionals published by Arthritis Research UK. In four practices, patients will receive the MOAC intervention, while the other four practices will continue to provide usual care. GPs in the intervention arm will be offered training for the initial consultation (MOAC 1), and practice nurses will be offered comprehensive training for follow-up consultations (MOAC 2), to deliver supported self-management of OA. The control practices will have the opportunity to receive the training at the end of data collection.

### The intervention

#### The MOAC intervention

In order to identify the content of the MOAC intervention, two consensus exercises with GPs, lay participants, practice nurses, community pharmacists, and allied health professionals (occupational therapists, physiotherapists, podiatrists) have been conducted [14,15]. Using the findings of these exercises and theoretical models to guide self-management (WISE) and support patient behaviour change, a three-stage consultation has been proposed. The MOAC intervention comprises of MOAC 1 (initial consultation with GP), MOAC 2 (follow-up visits with practice nurse) [37], and MOAC 3 (dissemination to other HCPs). Consultations will be recorded in the general practices through the use of the joint pain and OA consultation template (Additional file 3 provides the full details of the intervention).

### The OA Guidebook

The Arthritis Research UK Primary Care Centre at Keele University has developed a guidebook for patients and professionals to use as an aid to support self-management for OA, and this will be used in MOAC [38]. The OA Guidebook contains both evidence-based biomedical information and lay experiential knowledge about the nature of OA, how it is diagnosed and treated, and the ways in which people who have OA continue to keep going in their everyday lives. Together these will give patients insight into the rationale for the advice and treatments offered in MOAC 1, 2 and 3 and what, practically, people who have OA have found helpful in learning to live with the condition. The patient guidebook will be a useful way to reinforce verbal information given by HCPs, to act as a resource to consult if queries or uncertainties arise in the future, to help structure MOAC 2 consultations, and to prompt questions to ask HCPs.

### The training

Training and educational packages will be developed for GPs and practice nurses by drawing on the work of Michie et al. [29,30]. GPs will receive training on how to deliver the initial consultation (MOAC 1) for a new or established patient consulting with OA and the procedure for referring to a practice nurse for a follow-up OA consultation (MOAC 2). Practice nurses will receive training in how to support and enable patients to self-manage OA, using a patient-centred approach, an OA guidebook, goal setting, pain management and the core NICE recommendations (information and advice, strengthening exercise and aerobic fitness training, and weight management). Nurses will also receive training in how to complete the MOAC 2 case report form (CRF), which will be completed for each patient attending the MOAC 2 consultations. Full details of these training packages will be published separately.

For MOAC 3, members of the wider multidisciplinary team linked to the intervention practices (*e.g*., physiotherapists, occupational therapists, podiatrists, pharmacists) will be invited to workshops to increase awareness of the study and its aims.

### Sample size

Published research in musculoskeletal disorders has estimated a minimal clinically important difference (MCID) from 2 to 4 points for the SF-36 version 2 Physical Component Summary (PCS) subscale [39], which has a normalised population standard deviation (SD) of 10. Hence, a difference between groups of 0.3 of an effect size is considered a minimum clinically important difference (MCID) threshold for the purposes of demonstrating superiority in the MOSAICS RCT.

In total, 500 patients will need to be recruited in expectation that 400 will provide data at six months. A total of 400 participants (200 to each arm) will ensure 90% power to detect at least the effect size of 0.3 at the primary time point of six months follow-up given a 5% two-tailed significance level. Randomisation is by practice, so this sample size calculation was inflated to correct for an intracluster correlation coefficient (adjusted ICC of 0.005), varying practice size recruitment was taken into account (including coefficient of variation of 0.5 as per POST trial [ISRCTN40721988]) and inclusive of (×0.67) and × 1.25 respective adjustments for repeated-measures design and 20% dropout allowance.

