### Analysis

#### Analysis of the cluster RCT

Baseline characteristics will be compared between treatment arms and presented at the level of: (i) GP-Practice clusters, and (ii) Patient characteristics.

Baseline data for GP-Practice characteristics will include data on the stratification variables for randomisation – *i.e*., practice list size and the number of GP practitioners, median index level of deprivation for the Practice, mean age and gender profile of the Practice populations. Baseline data for patients will include data pertaining to participants’ demographic characteristics, joint problem, management of their joint problem, general health and quality of life.

Balance of baseline characteristics is particularly important to establish for cluster trials given the higher level unit of randomisation and thus the potential for bias in the selection and recruitment uptake of patients. No formal statistical testing will be carried out for differences in baseline characteristics except for the GPAQ communication sub scale [49], as this is measure of the uptake of the model OA consultation by GPs.

Descriptive statistics on mean scores for numerical outcomes and frequency counts and percentages for categorical data will be presented for outcome measures from the consultation questionnaire, stratified by study group (intervention or control). A Linear Mixed Model will be used to analyse primary outcome data (SF-12 PCS). Statistical testing of clinical and process outcomes between study groups will be performed using regression methods (adjusting for age, gender, baseline SF12-PCS and corresponding baseline value, of the outcome being measured, as covariates at the individual-patient level and practice size as a covariate at the practice level). A 3-level mixed-model (linear- or generalised- as appropriate to numerical and categorical outcome data, respectively) will be fitted to test for the effect of the MOAC intervention from baseline across follow-up, taking into account clustering by practice (level 3) and patient (level 2) and repeat follow-up measures (level 1). P-values and 95% Confidence Intervals will be provided with estimates of effect size in the analysis of follow up data. The mixed model assumes that missing data is at least missing at random (MAR). We will examine effect estimates in relation to the indicated clinical marker of 0.3 of an effect size.

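### The stated 90% power rests on normal quantiles; allowing for the few degrees of freedom from eight randomised practices gives about 73–76% on a practice-level t reference

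*Protocol article*

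**What the plan says.** The Sample size section of the protocol article sets the target difference: "a difference between groups of 0.3 of an effect size is considered a minimum clinically important difference (MCID) threshold". It works on a scale "which has a normalised population standard deviation (SD) of 10", so 0.3 corresponds to 3 points. The power claim is "A total of 400 participants (200 to each arm) will ensure 90% power to detect at least the effect size of 0.3", "given a 5% two-tailed significance level".

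The section then lists its adjustments. The sample size was "inflated to correct for an intracluster correlation coefficient (adjusted ICC of 0.005"), and unequal recruitment across practices was allowed for, "including coefficient of variation of 0.5 as per POST trial". A factor of 0.67 is applied for repeated measures and 1.25 for dropout. No adjustment is listed for the number of practices or for degrees of freedom.

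The section on study component 1 describes a "two-arm prospective pragmatic cluster RCT based in eight general practices", with four practices in each arm and allocation stratified by list size. The section Analysis of the cluster RCT plans a three-level mixed model with practice at the top level and "practice size as a covariate at the practice level". It names no degrees-of-freedom method, which an article may leave to the analysis plan.

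**The concern.** A design effect corrects the variance of the arm comparison. It does not correct for having to estimate the between-practice part of that variance from only eight units. If the comparison is referred to between-practice variation, it has 8 − 2 = 6 degrees of freedom, or 5 after one practice-level covariate. The 5% critical value is then 2.45 or 2.57 instead of 1.96. With so few clusters the difference in power is material.

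The figure concerns the primary outcome and the trial's own threshold for a worthwhile effect. A reader who trusts 90% would put the chance of missing a true 0.3 SD effect at 1 in 10. On the t reference it is about 1 in 4. A non-significant result could then be taken as stronger evidence against a 0.3 effect than it is.

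**Working it through.** **Inputs**

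- From Sample size: effect 0.3 SD; two-sided 5%; 90% power; 200 analysed per arm; ICC 0.005; coefficient of variation 0.5; repeated-measures factor 0.67; dropout factor 1.25.
- From study component 1: eight practices, four per arm. Mean analysed per practice is therefore 400/8 = 50.
- From Analysis of the cluster RCT: one practice-level covariate.
- Assumed, because the article does not print its formula: the usual design effect for unequal clusters, and the 0.67 factor applied to the total variance.

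**1. Reproducing the plan's figure**

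- Individually randomised size per arm: 2 × (1.96 + 1.2816)² / 0.3² = 233.5.
- Design effect: 1 + [(1 + 0.5²) × 50 − 1] × 0.005 = 1 + 61.5 × 0.005 = 1.3075.
- Per arm: 233.5 × 0.67 × 1.3075 = 204.6. That is 409 in total, and 511 after × 1.25.

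The stated 400 and 500 are within 3% of these figures, so the method is normal quantiles with a design effect.

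**2. Power at 200 per arm with a normal reference**

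- Standard error: √(2 × 0.67 × 1.3075 / 200) = 0.0936 SD.
- Non-centrality: 0.3 / 0.0936 = 3.205.
- Power: Φ(3.205 − 1.96) = 89.3%.

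**3. Same standard error, non-central t on between-practice degrees of freedom**

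| Reference | Critical value | Power for 0.3 SD | Effect detectable with 90% power |
|---|---|---|---|
| Normal | 1.96 | 89.3% | about 0.30 SD |
| t, 6 df (8 practices − 2 arms) | 2.45 | 76.1% | about 0.37 SD |
| t, 5 df (also less practice size) | 2.57 | 72.7% | about 0.38 SD |

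On a standard deviation of 10, the last two detectable effects are about 3.7 and 3.8 points.

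**4. Simulation at the plan's inputs**

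- Equal practices at the same design effect, t test on 6 df: 76.2% power, 5.0% type I error.
- Equal practices, REML with Satterthwaite-type df: 76.4% power, 4.1% type I error.
- Equal practices, REML with a z reference: about 86% power, about 5.6–5.7% type I error.
- Practice sizes varying with coefficient of variation 0.5: a weighted cluster-level t test has 75.8% power and an unweighted one 70.5%.

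**5. Sensitivity to assumptions not given in the article**

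- Power at 6 df / 5 df for other ICC values: 0.001 gives 84% / 81%; 0.01 gives 67% / 64%; 0.02 gives 54% / 51%. At ICC 0 these t references still give only 86% / 83%.
- If the 0.67 factor shrinks only the within-practice variance, power is 86% by z, 72% on 6 df and 68% on 5 df.

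**The case against.** The strongest reply is that 5 or 6 degrees of freedom is one choice of reference, and a conservative one here. The article specifies a mixed model, not a comparison of eight practice means. At ICC 0.005 with 50 patients per practice, nearly all the variance lies within practices. In simulation the practice variance was estimated as zero in roughly 40–47% of runs, and the z test's type I error was only slightly inflated. If the critical value is raised just enough to give exactly 5% error at that ICC, equal practices give about 85–86% power. With varying practice sizes and the practice-size covariate, the figure is about 77–80%.

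Much of this stands. A reader might infer that every valid 5% test has 73–76% power, and the document does not support that: it names no degrees-of-freedom method, and the size of the shortfall depends on the test. The calibrated figure has its own limit, because it assumes the ICC is known to be 0.005. A fixed cut-off chosen that way would not hold the error at larger ICCs. The t reference does not need that knowledge.

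A reader might also infer that the calculation ignores clustering. It does not. The ICC and the variation in practice size are both in the design effect, and the mean cluster size of 50 follows from the eight practices. Only the small-sample degrees of freedom are absent.

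Nor do ICC values of 0.01–0.02 come from the article. They illustrate sensitivity and add nothing to the seriousness of the point.

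Finally, the risk of over-reading a null result is partly handled already. The analysis section plans 95% confidence intervals and an examination of effect estimates against 0.3.

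None of this restores 90%. An analysis plan that names a degrees-of-freedom method would not do so either, since the tests examined fall short with or without a correction.

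**Conclusion.** The concern holds as a misstated power figure. The 90% is a normal-quantile result (89% at 200 per arm) that allows for the variance inflation from clustering but not for the few degrees of freedom from eight practices.

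At the plan's inputs, power for 0.3 SD is about 76% (6 df) or 73% (5 df) on a practice-level t reference, and possibly about 70% with unequal practices. An uncorrected mixed-model z test has about 86%, but it is not a strict 5% test.

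These figures rest on ICC 0.005, a coefficient of variation of 0.5, 50 analysed per practice, and the 0.67 factor applied to the total variance. The direction is secure; the exact size depends on the test adopted. The design, the allocation and the choice of analysis model are not shown to be wrong.

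**What to change.** Change the wording of the Sample size section:

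- Say that the 90% rests on normal quantiles with a design effect.
- Restate power for 0.3 SD at ICC 0.005 as about 76% on a t reference with 6 df, or about 73% with the practice-size covariate (5 df). Note that unequal practice sizes may lower this to about 70%, and that an uncorrected z reference gives about 86% without strictly holding 5%.
- State that the effect detectable with 90% power on the t reference is about 0.37–0.38 SD.
- Label any ICC sensitivity as an assumption, for example 67% / 64% (6 df / 5 df) at ICC 0.01.

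In Analysis of the cluster RCT, add one sentence to the existing plan for confidence intervals and comparison with 0.3: a non-significant result will be judged by whether the interval excludes 0.3.

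The cost is text only, with a less favourable power statement. No added recruitment is needed. The Trial status section reports that all eight practices are recruited and the intervention delivered, so the change affects interpretation, not conduct.
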